### Procedures

During the protocol period, all patients admitted to the oncology ward who are identified and meet the eligibility criteria will be invited to participate in the study by the evaluating physiotherapist. These eligible patients will be informed about the objectives of the study and invited to sign the informed consent form. Next, the patients will be evaluated regarding anthropometric and clinical characteristics, fatigue, and mobility, as well as the occurrence, frequency, intensity, and discomfort of the main adverse effects of chemotherapy. After the initial assessment, patients will be randomized into an intervention group, which will perform aerobic exercise sessions, and a control group, which will receive a booklet with guidelines (the same booklet will be given to the patients in the intervention group). The next day, the intervention will begin. Aerobic training will be carried out from Monday to Friday while the patients are hospitalized for the chemotherapy cycle in the oncology ward. Before carrying out the day’s aerobic exercise session, the patients will be asked if they feel any type of discomfort that is related to the previous day’s training (for example, muscle or joint pain in the lower limbs). If for any reason chemotherapy is interrupted for a patient, the exercises will also be interrupted, and as soon as chemotherapy treatment is resumed, the exercise will also be resumed. The booklet will be given to the patients and explained by a trained physiotherapist. Patients will be re-evaluated on the day following the last day of the chemotherapy cycle regarding the occurrence, frequency, intensity, and discomfort of adverse effects of the treatment, as well as fatigue, mobility, and satisfaction with the proposed intervention.

After the study intervention period, patients who need it will receive routine physiotherapeutic care provided by the physiotherapy team at the hospital. The incidence of clinical complications from chemotherapy and the length of hospital stay will be assessed as outcomes until hospital discharge. All data will be collected by a blinded assessor. Additionally, data will be coded and entered into a Microsoft Excel spreadsheet and will be double-checked before analysis. A visual representation of the study design is presented in Figure 1.

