The adverse effects of aerobic training, such as muscle pain, will be collected in the form of a question, developed by the researchers themselves, that will be answered every day before starting a new aerobic exercise session. In the same way, the patients’ subjective perception of satisfaction and discomfort in relation to the proposed protocol will be assessed through 2 questions developed by the researchers themselves that will be answered on the day of the patients’ final assessment. The patients’ responses to the questions will be on a scale of 0 to 10. In the question about satisfaction with the treatment, 0 will indicate “complete dissatisfaction” and 10 “maximum satisfaction.” When the question is about the discomfort of the treatment, 0 will indicate “no discomfort” and 10 will indicate “maximum discomfort.”

At the end of the treatment, the acceptability, suitability, and feasibility outcomes will be assessed using the Weiner scale [26], which was translated and adapted into Brazilian Portuguese [27]. The answer options for all questions are “completely disagree” (1 point), “disagree” (2 points), “neither agree nor disagree” (3 points), “agree” (4 points) and “completely agree” (5 points).

Acceptability is the perception among parties interested in implementing a given treatment that it is pleasant or satisfactory. It will be evaluated in terms of patient satisfaction in the intervention group according to their responses to the following statements: (1) “Physical exercise during chemotherapy treatment has my approval”; (2) “Physical exercise during chemotherapy treatment is attractive to me”; (3) “I enjoyed physical exercise during chemotherapy treatment”; and (4) “I recommend physical exercise during chemotherapy treatment.”

As for suitability, it is the relevance or compatibility of the proposed innovation (ie, treatment) for a given clinical practice environment. It will be evaluated by the following statements addressed to health professionals who care for patients included in this study, such as doctors, nurses, and physiotherapists: (1) “Physical exercise during chemotherapy treatment seems appropriate”; (2) “Physical exercise during chemotherapy treatment seems adequate”; (3) “Physical exercise during chemotherapy treatment seems applicable”; and (4) “Physical exercise during chemotherapy treatment seems to be a good option.”

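### Having a blinded assessor collect all data conflicts with intervention-only acceptability items and a daily training-effect question, which reveal the patient's arm and, with room allocation, the roommates' arm

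*Protocol article*

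**What the plan says.** The Procedures section of the protocol article ends its account of data collection with "All data will be collected by a blinded assessor". Its list for the re-evaluation after the cycle covers treatment side effects "as well as fatigue, mobility, and satisfaction with the proposed intervention".

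The Assessments section requires a blind evaluator, scale by scale, for the Memorial Symptom Assessment Scale (MSAS-BR, primary), the Brief Fatigue Inventory (BFI) and the DEMMI. It then adds further items without saying who collects them:

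- **Daily training effects:** a question "that will be answered every day before starting a new aerobic exercise session".
- **Satisfaction and discomfort:** "2 questions developed by the researchers themselves that will be answered on the day of the patients’ final assessment".
- **Acceptability:** "At the end of the treatment, the acceptability, suitability, and feasibility outcomes will be assessed using the Weiner scale". Of acceptability it says: "It will be evaluated in terms of patient satisfaction in the intervention group according to their responses to the following statements". One of these statements is "I enjoyed physical exercise during chemotherapy treatment".

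The Randomization section allocates rooms of 2 to 4 beds, one group per room. It says the evaluator is blind while patients and the treating physiotherapist are not, and it has the evaluator's guess of each patient's group recorded after the assessments. The Interventions section gives two safeguards for blinding: the same booklet for both groups, and removal of the ergometer from the room after each session.

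**The concern.** Two stated rules pull against each other. One gives every item to a blind person. The other includes items that cannot be collected without knowing, or learning, the arm. Neither safeguard in the Interventions section touches the questionnaires.

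The evaluator is the only blinded party when outcomes are measured. The DEMMI is scored by that person from observed performance. Complications are taken from medical records, but deciding that one arose from chemotherapy can call for judgement. These are the outcomes that knowledge of the arm could shift. Room allocation widens the problem beyond the patient being interviewed.

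**Working it through.** There is no figure in the plan to reproduce for this point. The check is a comparison of who collects which item, from whom, and what it gives away.

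| Item | Put to | Collector named in its own description | Reveals the arm? |
|---|---|---|---|
| MSAS-BR, BFI, DEMMI | Both arms | Blind evaluator | Not by design |
| Complications, intensive care transfer, length of stay | Both arms, from records | None; covered by the Procedures sentence | Not by design |
| Satisfaction and discomfort, 0 to 10 | Not limited to one arm | None | The question need not; the answer may |
| Acceptability | Intervention arm only | None | Yes |
| Daily training-effect question | Patients about to exercise | None | Yes |
| Feasibility, patient part | Patients in the study; not limited to one arm | None | Possibly, since the statements name exercise |

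**Step 1: the acceptability items.** To give a form to the intervention group only, the person giving it must know who is in that group. A blind assessor would have to be told the arm beforehand, and a control patient is then identified by not getting the form. The wording of the enjoyment statement gives the same information.

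**Step 2: the daily question.** Only patients with training sessions have a question tied to the start of a session. Whoever asks it knows the arm.

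**Step 3: the spread to roommates.** One allocation covers the room, so knowing one patient's arm gives the arm of everyone else enrolled there. With 2 to 4 beds:

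- smallest room: 2 − 1 = 1 roommate
- largest room: 4 − 1 = 3 roommates

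This assumes that the other beds hold trial patients whose stays overlap. If a room keeps its allocation over time, later occupants are exposed too. The article does not say whether it does.

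**Step 4: whether order solves it.** The order of items on the final day is not stated. Placing the revealing items last would protect the interviewed patient's own DEMMI. It would not protect a roommate assessed later, because the assessor would arrive already knowing the room's group.

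**The case against.** The strongest reply is that the sentence is a general one and was not meant literally. It follows directly after complications and length of stay, so it may refer to outcome data. The blind evaluator is named separately for MSAS-BR, BFI and DEMMI and for nothing in the later list. Vital signs and Borg scores are recorded during supervised sessions, which a blind assessor cannot do. The daily question comes just before those sessions, so the supervising physiotherapist probably asks it. A condensed article may also leave such duties to the full protocol.

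Much of this stands as an account of what the authors probably intend, and it makes the daily question weaker evidence than the acceptability items. It does not remove the conflict. The sentence has no exception, satisfaction is listed in the same re-evaluation as the outcomes, and no other collector is named for the acceptability items. This is a stated rule that defeats another stated rule, not an omitted detail.

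A reader might infer more than the documents support:

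- **That a large, known share of patients is exposed.** With 10 permanently allocated rooms, for example, the share could reach (94 − 10)/94 = 89%; with 6 rooms it would be 94%, and with 20 rooms 79%. The article gives neither the number of rooms nor the permanence of their allocation. The sum also requires one patient per room to be assessed before all the others.
- **That the satisfaction question itself unblinds.** It concerns the proposed intervention or treatment, is not limited to one arm, and both arms receive a booklet.
- **That the primary outcome loses its protection.** MSAS-BR and BFI are ratings by patients who know their arm, so the assessor's knowledge adds comparatively little.
- **That the check of the assessor's guess becomes worthless.** It would detect this leak; what it cannot do is prevent it.

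**Conclusion.** The point holds in a limited form. If the Procedures sentence is followed as written, the person who must be blind collects items that disclose the arm, and allocation by room carries that knowledge to 1 to 3 roommates not yet assessed. The roommate range rests on the stated bed numbers and on overlapping stays of trial patients. Wider exposure would need fixed room allocations, which are not stated.

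The main exposure is the DEMMI and the judgement of complications, with a smaller effect on MSAS-BR and BFI. The documents do not show that blinding has failed in practice. They show that the written instruction would break it. Since the remedy is cheap and recruitment is described as ongoing, the text should be corrected.

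**What to change.** 1. Limit the sentence in Procedures to the outcomes that must be blind: MSAS-BR, BFI, DEMMI, EQ-5D-3L, and the record-based outcomes (complications, intensive care transfer, length of stay). The record-based outcomes must stay in the list; a shorter one would drop blinded collection of exactly the outcomes described just before that sentence.
2. Have satisfaction, discomfort, acceptability, patient feasibility and the daily training-effect question collected by the already unblinded physiotherapist or by sealed self-completion. The end-of-treatment items should come after the blinded assessment. All of these items should be on forms that the assessor does not see at any time, so that roommates are protected as well.
3. Record the assessor's guess of each patient's group, and give no feedback on it until the trial ends.

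The cost is the reassignment of a few questions between people already on the study. The downside is possible courtesy bias when patients rate satisfaction and acceptability to the physiotherapist who trained them; sealed self-completion reduces it. With recruitment under way, the change protects only the assessments still to come.

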**Figure 1 figure1:**
[figure not shown]
Clinical trial flowchart. BFI: Brief Fatigue Inventory; DEMMI: De Morton Mobility Index; MSAS-BR: Memorial Symptom Assessment Scale, Brazilian version.

### Randomization

Immediately after baseline assessments and before starting the intervention, patients will be randomly allocated to 1 of 2 groups: intervention or control. The allocation will be conducted by a researcher who will not be involved in the selection or evaluation of patients or in the intervention; it will follow a randomization schedule generated by a website [16] with a 1:1 allocation rate. The rooms in the ward accommodate 2 to 4 patients (beds); therefore, randomization will be carried out by group or cluster [17]. The rooms will be randomized, because although the intervention is directed to one patient, it can affect another patient in the same room, contaminating those who should not receive the intervention and reducing the estimated result [17]. The researcher responsible for randomization will place a written document inside a sealed opaque envelope indicating which group (intervention or control) each room belongs to in order to ensure the confidential allocation of patients to the blinded evaluator [18]. Before starting the intervention, the physiotherapist responsible for the intervention will open the envelope in front of the patient and disclose which group the room the patient is in corresponds to.

Due to the nature of the study, it will not be possible to blind the physiotherapist responsible for the intervention or the patients. However, the evaluator will be blinded to the groups (intervention and control). After the intervention and assessments, the physiotherapist responsible for the intervention will ask the blinded evaluator to which group (intervention or control) he believes each patient belonged to evaluate the evaluator’s blinding.

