## Methods

### Design

This is the protocol for a randomized controlled trial with 2 parallel groups, 1:1 allocation, and blind evaluation that will be conducted in the oncology ward of the Instituto de Assistência Médica ao Servidor State Public, São Paulo-SP, Brazil, in accord with the CONSORT (Consolidated Standards of Reporting Trials) checklist [12]. The trial has been registered on the Registro Brasileiro de Ensaios Clínicos (RBR-6b4zwx3).

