### Statistical Design

The calculation to determine the sample size was carried out based on a previous randomized clinical trial that also compared the effect of aerobic training compared to usual care on the deleterious effects of chemotherapy in patients with breast cancer [11]. Our study was designed to detect a difference of 2.7 (SD 4) points in the physical fatigue score, in addition to a difference of 6.2 (SD 7) episodes of vomiting or nausea between the groups. A power of 80%, an α of 5%, and a loss to follow-up of 15% of the sample were considered. A sample of 94 patients (47 patients in each group) was estimated.

After the data collection, all analyses will be conducted following intention-to-treat principles and will be performed by a researcher who will not be involved in the study assessments and intervention.

For analyzing the effect of the intervention, after a descriptive analysis and the Shapiro-Wilk normality test with a visual analysis, the groups will be compared using a linear mixed model for fatigue, mobility, and chemotherapy-related symptoms before and after the intervention. The length of hospital stay will also be compared between groups using Kaplan-Meier survival analysis. The *χ*^2^ test will be used to compare the clinical complication rates between groups. Descriptive analysis will be used for recruitment, completion, and adherence rates and potential adverse events. The significance level will be set at 5%. For all these analyses, SPSS (version 21.0; IBM Corp) will be used.

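### Rooms are randomised as clusters, but the sample size has no design effect and the named analyses do not account for the room

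*Protocol article*

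**What the plan says.** The Randomization section of the protocol article makes the room the unit of allocation: "The rooms in the ward accommodate 2 to 4 patients (beds); therefore, randomization will be carried out by group or cluster". Its reason is contamination: "The rooms will be randomized, because although the intervention is directed to one patient, it can affect another patient in the same room". The sealed envelope names the group of a room, and the schedule is described thus: "it will follow a randomization schedule generated by a website [16] with a 1:1 allocation rate". Elsewhere the wording is that of individual allocation. Procedures and the opening of Randomization speak of patients being randomised after their baseline assessment. The Design section calls the study a "randomized controlled trial with 2 parallel groups, 1:1 allocation, and blind evaluation" without naming the unit.

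Statistical Design sizes the trial on two targets: a fatigue difference of 2.7 (SD 4) and a nausea/vomiting difference of 6.2 (SD 7) episodes. It adds 80% power, 5% alpha and 15% loss, and concludes: "A sample of 94 patients (47 patients in each group) was estimated". No ICC, cluster size, number of rooms or design effect appears.

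The named analyses are:
- a linear mixed model of symptoms, fatigue and mobility before and after the intervention;
- for length of stay, "The length of hospital stay will also be compared between groups using Kaplan-Meier survival analysis";
- for complications, the chi-square "test will be used to compare the clinical complication rates between groups".

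The economic evaluation uses a bootstrap with 5000 replications. None of these mentions the room.

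**The concern.** When rooms are allocated, the evidence about the treatment comes from the contrast between rooms. Patients in one room share surroundings, ward routine and one another's company, so their outcomes may be correlated. An analysis that counts them as independent then credits the trial with more information than it has: standard errors are too small, intervals too narrow, and a true null is rejected more often than 5% of the time. Spare sample size does not cure this, because the error lies in the variance and not in the number of patients. Separately, a power figure derived for independent patients does not describe a room-randomised trial. A critical reader could set the results aside as a unit-of-analysis error.

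**Working it through.** **Inputs from Statistical Design.** Fatigue d = 2.7/4 = 0.675; nausea/vomiting d = 6.2/7 = 0.886; power 80%; alpha 5% (two-sided assumed, as sidedness is not stated); loss 15%; 47 per arm. Evaluable per arm: 47 × 0.85 = 39.95, taken as 40.

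**Assumptions.** ICC 0.05 to 0.10, as the article gives none. Enrolled patients per room m = 2, 3 or 4, matching the bed numbers.

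**Step 1: the plan's own figure.**
- Fatigue: n per arm = 2(1.960 + 0.842)²/0.675² = 34.5, so 35 (36 with the t distribution). Divided by 0.85: 42 or 43 per arm, total 84 or 86.
- Nausea/vomiting: 21 or 22 per arm, total 50 or 52.

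The stated 94 is not reproduced. It exceeds the fatigue requirement by a factor of 94/86 = 1.09 to 94/84 = 1.12. The article does not explain this excess and nowhere calls it a design effect.

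**Step 2: type I error if the room is ignored.**
Design effect DE = 1 + (m − 1) × ICC. Type I error = 2 × [1 − Φ(1.96/√DE)]. Example, m = 3 and ICC 0.10: DE = 1.20, 1.96/√1.20 = 1.789, error 7.4%.

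**Step 3: power of a test that respects the room.**
Two-sample t power with 40/DE per arm. The second figure in each power cell uses room-level degrees of freedom, 2 × 40/m − 2.

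| m | ICC | DE | Type I error, room ignored | Fatigue power: DE only / room df | Nausea/vomiting power: DE only / room df |
|---|---|---|---|---|---|
| 2 | 0.05 | 1.05 | 5.6% | 83% / 82% | 97% / 96% |
| 2 | 0.10 | 1.10 | 6.2% | 81% / 80% | 96% / 96% |
| 3 | 0.05 | 1.10 | 6.2% | 81% / 79% | 96% / 95% |
| 3 | 0.10 | 1.20 | 7.4% | 77% / 75% | 95% / 93% |
| 4 | 0.05 | 1.15 | 6.8% | 79% / 76% | 95% / 94% |
| 4 | 0.10 | 1.30 | 8.6% | 74% / 71% | 93% / 91% |

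With independent patients, 40 per arm gives 85% power for fatigue and 97% for nausea/vomiting.

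**Step 4: how much clustering the 94 can absorb.** By the t calculation, 80% fatigue power needs 35.44 effective patients per arm, so the largest tolerable DE is 40/35.44 = 1.13. A normal approximation gives 1.16. Room-level degrees of freedom lower this margin.

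**Step 5: if a room keeps its allocation.** Clusters then grow beyond the bed number. As an illustration only, 5 rooms per arm with 8 evaluable patients each give DE 1.35 to 1.70 and a type I error of 9.2% to 13.3% at ICC 0.05 to 0.10. The article does not say whether a room is randomised once or at each new occupancy.

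**The case against.** **Power need not fall below 80%.** A reader might infer that the trial is underpowered. The documents do not show that. The 94 contains slack over its own inputs. At 2 patients per room, fatigue power is still about 80-81% at ICC 0.10. The nausea/vomiting target, which is closer to the symptom-based primary outcome in the Assessments section, stays above 90% throughout the table; fatigue is listed there among the other outcomes. This stands.

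**Not every planned analysis is shown to be wrong.** A linear mixed model can carry a room effect and a bootstrap can resample rooms; an analysis plan that is not shown might specify both. This also stands. The firm part is the sample size and the chi-square and Kaplan-Meier comparisons as named. For the mixed model, one can say only that it is tied to before/after measurement with no room term stated.

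**The stated rationale is contamination, not correlation.** The Randomization section worries about the intervention reaching roommates and diluting the effect. That is not a statement that outcomes correlate within rooms, and it should not be read as one. But once rooms are allocated, independence within rooms becomes an assumption, and the plan neither states nor defends it.

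**The true inflation may be small.** Beds are not participants, so enrolled clusters may be smaller than the rooms. At 2 per room and ICC 0.01 the type I error is only 5.1%. Equally, successive patients in a fixed room would make it larger. The size is unknown in both directions.

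**Conclusion.** The concern holds in this form: allocation is by room, the sample size makes no allowance for it, and two of the named comparisons assume independent patients. For any positive ICC, following them as written gives a type I error above 5%: about 5.6% to 8.6% for 2 to 4 patients per room at an assumed ICC of 0.05 to 0.10, and more if rooms accumulate patients. The 80% power is unsupported for a room-randomised design, which is weaker than saying that it fails. Over the same range, fatigue power is about 83-74% by design effect alone and 82-71% with room-level degrees of freedom. These figures rest on assumed ICCs and cluster sizes, a two-sided test and 40 evaluable patients per arm. The five-rooms-per-arm case illustrates direction only and is not an estimate for this ward.

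**What to change.** 1. Record each patient's room and the occasion on which that room was allocated, if this is not already done. Recruitment is ongoing, and the information may be hard to recover later.
2. Add a random intercept for the randomised room to the linear mixed model, with small-sample (Satterthwaite or Kenward-Roger) degrees of freedom.
3. Replace the chi-square test with a mixed logistic model with a room effect, a GEE with small-sample correction, or a permutation test over rooms.
4. Compare length of stay with a room-clustered or shared-frailty time-to-event method. Kaplan-Meier curves can stay as description. The article assigns the clinical analyses to SPSS and only the economic evaluation to Stata, so the software statement may need to change.
5. Resample rooms, not patients, in the bootstrap.
6. Restate the power of the 94 patients for both sizing targets over a stated range of ICC and cluster size, with the number of rooms, and say whether a room is randomised once or per occupancy.
7. Reconcile Design, Procedures and Randomization on the unit of randomisation.

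The cost is analysis wording, one or two data fields, wider intervals and a lower stated power. The change itself needs no extra patients. How far power falls depends on the number of rooms and could be more than slight if few rooms hold a fixed allocation.

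### Rooms are randomized and their arm is disclosed at the bedside while admissions continue, so concealment cannot be assured for patients who enter an already disclosed room

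*Protocol article*

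**What the plan says.** All places are in the Methods of the Protocol article.

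- **Order of events.** Randomization opens with a patient-level statement: "Immediately after baseline assessments and before starting the intervention, patients will be randomly allocated to 1 of 2 groups". Procedures gives the same order, with the initial assessment first and randomization afterwards.
- **Unit.** Randomization then notes that rooms have 2 to 4 beds and concludes: "therefore, randomization will be carried out by group or cluster". The reason given is contamination between patients who share a room.
- **Envelope.** The sealed, opaque envelope holds a document "indicating which group (intervention or control) each room belongs to". It carries the arm of a room, not of a patient.
- **Disclosure.** Before the intervention starts, the physiotherapist delivering it is to "open the envelope in front of the patient and disclose which group the room the patient is in corresponds to".
- **Recruitment.** Procedures describes a rolling intake: "all patients admitted to the oncology ward who are identified and meet the eligibility criteria will be invited to participate". These patients "will be invited to participate in the study by the evaluating physiotherapist".
- **Safeguards.** The researcher who allocates has no part in selection, evaluation or intervention. The evaluator is described as blinded, and the evaluator's guess of each patient's group is collected at the end (Randomization). Both arms receive the same booklet, and the cycle ergometer is taken out of the room after each session (Interventions).

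**The concern.** An envelope protects against selection only until it is opened. Here one opening settles the arm for a shared room, and patients continue to be admitted to the ward. A patient who enters the room later is invited, consents and reports baseline symptoms when the arm of that room has already been disclosed to the treating physiotherapist and to at least one roommate. The stated sequence of baseline first and allocation second cannot hold for that patient.

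Entry into the trial can then depend on the arm. Patients who like or dislike the idea of exercise may accept or decline differently in the two kinds of room. The symptom scale (MSAS-BR) and the Brief Fatigue Inventory are self-reported, so baseline scores may also shift once the arm is known. Intention-to-treat analysis and the linear mixed model named in Statistical Design work on the patients who entered. Neither corrects for differential entry.

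**Working it through.** **1. The passages side by side.** Under the room-level procedure, allocation follows baseline only for participants who had already been assessed when the room's envelope was opened. For everyone who enters under that envelope afterwards, allocation precedes consent and baseline. The patient-level and room-level descriptions agree only if nobody joins a room after opening, and nothing in the article ensures this.

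**2. Inputs for the size.** The plan gives no figure for the share affected. The total of 94 (Statistical Design) serves only as a denominator here; how it was derived does not bear on this point. The article states neither the number of rooms k nor whether a room keeps its arm, so both are assumptions.

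**3. Case A: each room keeps its arm for the whole trial.** Assume every room contributes participants and exactly one per room is assessed before opening. The share entering after disclosure is (94 − k)/94.

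| Assumed k | After disclosure | Share |
|---|---|---|
| 4 | 90 | 95.7% |
| 10 | 84 | 89.4% |
| 20 | 74 | 78.7% |
| 30 | 64 | 68.1% |
| 46 | 48 | 51.1% |
| 47 | 47 | 50.0% |

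The share exceeds one half for any k below 47. If f participants per room are assessed before opening, it becomes (94 − f·k)/94. With k = 10, f = 2 gives 74/94 = 78.7% and f = 4 (a full four-bed room) gives 54/94 = 57.4%.

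**4. Case B: a new allocation is drawn each time a room fills.** With m participants per envelope, and only the first assessed before opening, the share is 1 − 1/m:

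- m = 1: 0%
- m = 2: 50%
- m = 3: 67%
- m = 4: 75%

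If all m are assessed before opening, the share is 0%.

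**5. What the shares count.** They count patients whose room's arm had been disclosed to someone before they entered. That is an upper limit on the number who knew the arm when they consented.

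**The case against.** The strongest reply is that a harsher reading goes beyond the text. A reader might infer that each room has a single envelope, opened once for its first patient and never renewed, so that concealment fails for most of the sample. The wording about the group a room belongs to makes this the natural reading, but the article does not say so, and a fresh draw at each filling is not excluded. Any unconditional percentage therefore rests on an assumption about the procedure as well as an assumed room count.

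A reader might also infer that the recruiting physiotherapist knows the arm. The article says the opposite: the evaluator is blinded, both arms get the booklet, and the ergometer is removed. A leak is likely, because the evaluator meets unblinded roommates and the removal of the ergometer implies that training takes place in the room. It is still not a documented fact. That beds are assigned with an eye to the arm is speculation, since bed assignment is not described, and an article may leave it to the full protocol.

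These objections limit the size and the wording. They do not remove the defect. The independent allocator and the envelope protect only up to the opening. The booklet and the removal of the ergometer are aimed at the evaluator and do not stop a new patient from learning the arm from a roommate. The end-of-study guess can detect unblinding but cannot prevent it. The article itself accepts that patients cannot be blinded and that what happens to one patient can affect another in the same room.

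**Conclusion.** The point holds in a conditional form. The statements that allocation follows baseline conflict with room randomization, bedside disclosure and intake on admission, and must be reconciled. Concealment cannot be assured for any patient who enters a room whose arm has already been disclosed.

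If rooms keep their arm, and one participant per room precedes disclosure, that is most of the sample for any ward with fewer than 47 rooms. If rooms are redrawn at each filling, the share lies between 0% and 75% for 1 to 4 participants per envelope. The documents do not settle which case applies. They do not support the flat statement that concealment fails for most patients, or that the evaluator knows the arm.

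**What to change.** 1. State one procedure. Draw a new sealed allocation from the list for each room-occupancy period, and open it only after all eligible occupants then present have consented and completed baseline.
2. Record for each patient whether the room's arm had already been disclosed at consent.
3. Prespecify a sensitivity analysis by that flag, excluding flagged patients where enough remain. If rooms have kept their arm so far, exclusion could leave very few: with 10 rooms and one participant each before opening, 10 of 94. A comparison of results by flag is then the workable form.
4. Report the numbers eligible, approached and declined by room arm.

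**Cost.** A longer list, more envelopes and a short wait before opening, which must fit the next-day start in Procedures. Some late joiners will remain, because rooms may seldom empty completely. The Results section says recruitment is ongoing, so item 1 would be a mid-trial change in procedure, to be documented with its date. Items 2 and 4 can start at once.
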